### Exclusion criteria

History of serious psychiatric or neurologic disorder: hallucination, delusion, abuse of or dependence on alcohol or drugs, cerebrovascular disease, or degenerative disease of the central nervous systemUse of medications related to HB, such as anti-depressants or anti-anxiety, during the preceding 1 monthA seriously unstable medical condition: needing active medical treatment promptly, abnormal vital signs, or intolerable pain or poor food intake causing difficulty in activities in daily living (ADL)Participation in other clinical trialsFemale participants who are pregnant, breast-feeding, or planning to become pregnantResidents of collective dwelling facilities, such as social welfare institutionsFailure to provide written informed consentLack of eligibility for the trial for other reasons: illiteracy, questionnaires are not understood or answered, or if the patient is not expected to be compliant with the treatment and evaluation visit schedule

## Intervention

### Intervention of experimental group

Ten acupuncture sessions will be conducted at fixed and individualized acupuncture points for 4 weeks by inserting an acupuncture needle perpendicular to the skin at a depth of 5.0–25.0 mm with manipulation for the *de-qi* and maintaining the position for 20 min each session. Disposable, sterile, 0.25 × 30-mm stainless steel acupuncture needles (Dongbang, South Korea) will be used. The fixed acupuncture points will be GV20, CV17, HT7, and ST36, and the individualized points will be decided according to the participants’ specific symptoms [24, 29, 30]. The locations of the acupuncture points are presented in the Standards for Reporting Interventions in Clinical Trials of Acupuncture (STRICTA) (Additional file 1). Qualified TKM doctors (KMD) with over 4 years of clinical experience will be in charge of the intervention.

### Treatment of control group

The CG will receive minimal acupuncture on non-acupuncture points 10 times over 4 weeks. The same type of acupuncture needle will be inserted perpendicular to the skin at a depth of 1.0–3.0 mm without manipulation for the *de-qi* and maintained for 20 min. The number of acupuncture points, duration, and frequency of the sessions will be the same as those for the EG, and the same practitioner will conduct the intervention.Location of non-acupuncture points:Upper extremities (UE) 1 (bilateral): 1 cm lateral from 5 cm below the midpoint of the transverse cubital creaseAbdomen 1: 3 cm lateral from a point 13.5 cm above the umbilicusLower extremities (LE) 1 (bilateral): 1.5 cm above EX-LE2 (the center of the upper border of the patella)LE 2 (bilateral): point at the upper one third of the medial part of the tibiaLE 3 (bilateral): 1.5 cm below LE 2

### Allowed or prohibited concomitant treatment

All treatments for HB and symptom management will be prohibited. Other subjects’ treatments for underlying chronic diseases will be allowed if they do not change during the study period. If a violation occurs during the study period, the patient will be removed from the study.

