### Setting of the study

This clinical trial will be conducted at the outpatient department of a university hospital. Public recruitment advertising will be used to recruit participants to voluntarily apply to the trial, and a Korean medical doctor (KMD) will explain the details of the trial and will supply documented explanations. When the participants decide to enroll in the trial, they will be asked to submit written consent and to undergo evaluation to ensure compliance with inclusion/exclusion criteria. Participants who are eligible for the study will be randomly assigned to one of two groups and will receive the planned intervention and evaluation according to their corresponding group. Both groups will receive the intervention for a total of 10 sessions for 4 weeks (two to three sessions per week). A post-treatment assessment will be performed at 4 weeks after visit 1, and the study will be completed 8 weeks after visit 1 (Fig. 1).

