### Statistical analysis

The recruitment rate, compliance rate, and completion rate will be presented as a number and percentage and will also be presented for each group. For clinical outcomes, including VAS scores for the core symptoms of HB and subjective anger, the BDI, the SRI-short form and serum serotonin levels, the mean SD at each assessment point and Cohen’s *d*, which is an estimated effect size that indicates the standardized difference between two mean values, will be presented [38]. Effect size will be calculated based on the value immediately after the end of the 4-week treatment (visit 10).

Analyses will mainly be performed using the full analysis set (FAS) population, while the per-protocol set (PPS) population will be analyzed as a supplement. Although the intention-to-treat (ITT) ideal includes all randomized subjects, the FAS approach acknowledges the practical infeasibility of completely following all participants until study completion and includes as complete and as similar a population to ITT as possible [39]. The FAS population does not include the following: (1) individuals who do not meet the inclusion criteria, (2) individuals who have never undergone acupuncture treatment, and (3) individuals who have never been assessed since randomization and, therefore, have no data available for collection. The PPS population will include the following: (1) individuals for whom acupuncture accounts for more than 80% of the total number of treatments received, (2) individuals who have had their evaluation parameters measured, and (3) individuals who do not violate the clinical trial protocol [40]. Missing data will be replaced by multiple imputation. Statistical analyses will be conducted by an independent statistician using SAS® version 9.4 (SAS Institute Inc., Cary, NC, USA).

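### The removal and dropout rules make no provision for continued outcome assessment of participants whom the main, ITT-like analysis does not exclude

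*Protocol article*

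**What the plan says.** All references are to the protocol article.

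- *Allowed or prohibited concomitant treatment*: "All treatments for HB and symptom management will be prohibited". The consequence of a breach is: "If a violation occurs during the study period, the patient will be removed from the study". The wording is the study, not the study treatment.
- *Criteria for dropout*: attendance below 80%, a violation of the trial plan, and medication that could influence the results are listed together with withdrawal of participation and loss of contact. The list does not say whether any of these people are still assessed.
- *Statistical analysis*: "Analyses will mainly be performed using the full analysis set (FAS) population". The per-protocol set (PPS) is supplementary. The FAS is described as one that "includes as complete and as similar a population to ITT as possible". It leaves out people who fail the inclusion criteria, people who were never needled, and "individuals who have never been assessed since randomization and, therefore, have no data available for collection". Poor attendance and deviation are not grounds for exclusion. The section adds: "Missing data will be replaced by multiple imputation".
- *Clinical outcomes*: the outcome measures are taken at baseline and weeks 3, 5 and 9. The effect size uses the value at the end of the 4-week treatment.
- *Feasibility outcomes*: acupuncture counts as acceptable for a full-scale trial if d exceeds 0.2 for three or more of the six symptom scores.

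**The concern.** The analysis section justifies the FAS on the ground that not everyone can in practice be followed to the end. Here follow-up appears to stop because a rule stops it. Someone who missed three sessions or took another remedy can usually still mark a VAS.

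The people concerned may well differ from the rest. Seeking other treatment or missing sessions is plausibly linked to how the participant is doing, and the pattern may differ between real and minimal acupuncture. Multiple imputation corrects only for what the observed data predict. At stake are the progression decision and the effect sizes that the *Discussion* says will inform the sample size of the full trial. No analysis plan can recover outcomes that were never collected.

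**Working it through.** **Step 1. Trace the rules into the analysis sets.**

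| Event | What the article says happens | Excluded from FAS? | Kept out of PPS? |
|---|---|---|---|
| Prohibited concomitant treatment | Removed from the study | No | Yes, as a protocol violation |
| Attendance below 80% | Dropout | No | Yes |
| Violation of the trial plan | Dropout | No | Yes |
| Any of these before week 3 | As above | Yes, if no outcome has been assessed since randomization | Yes |

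The PPS already separates low attenders and violators, so ending their assessments is not needed for that purpose. The effect on the FAS is mainly missing week 5 and week 9 values. Loss from the set itself affects only those removed before week 3.

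**Step 2. Inputs.**
- From the article: 26 participants (*Sample size calculation*); 1:1 allocation (*Background*), so 26/2 = 13 per arm; "Both groups will receive the intervention for a total of 10 sessions for 4 weeks" (*Setting of the study*), so the attendance limit is 0.8 × 10 = 8 and 7 or fewer sessions is dropout; progression threshold d > 0.2.
- Not in the article: a removal rate in either arm, and the outcome gap between removed and retained participants. Both are assumed below.
- There is no stated figure to reproduce. The 26 does not come from a power calculation and no dropout rate lies behind it.

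Each participant is 1/13 = 7.7% of an arm.

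**Step 3. Formula.** Let p_E and p_C be the shares removed in the acupuncture and sham arms. Let D be the amount, in SD units, by which the removed participants' true outcomes are worse than the values imputed for them. With benefit counted as positive,

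bias in d ≈ (p_E − p_C) × D.

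**Step 4. Results on assumed inputs.** A simulation checked the formula: 13 per arm, 20,000 replicates, baseline-outcome correlation 0.5, removal unrelated to baseline, imputation by regression on baseline within arm.

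| p_E | p_C | D | Formula | Simulation |
|---|---|---|---|---|
| 15% | 15% | 0.5 | 0 | −0.001 |
| 15% | 15% | 1.0 | 0 | 0.000 |
| 20% | 10% | 0.5 | 0.05 | 0.050 |
| 20% | 10% | 1.0 | 0.10 | 0.097 |
| 10% | 20% | 0.5 | −0.05 | −0.051 |
| 10% | 20% | 1.0 | −0.10 | −0.100 |
| 25% | 5% | 1.0 | 0.20 | 0.201 |
| 5% | 25% | 1.0 | −0.20 | −0.201 |

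More removal from the acupuncture arm flatters acupuncture; more from the sham arm works against it. The simulation filled in fitted values rather than multiple draws, which changes the spread but not the average bias. It did not use week 3 values. Where those predict the later outcome, D is smaller.

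**Step 5. Scale.** At d near 0, the standard error is √(2/13) = 0.392 and the 95% half-width is 1.96 × 0.392 = 0.77.

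**The case against.** Several points on the other side are sound.

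- A reader might infer that all three groups are expressly removed from the study. They are not. Those words cover concomitant-treatment breaches only; low attendance and plan violations are called dropout, and the full protocol may say what follows. The PPS also lists attendance and having measurements as separate conditions, which is compatible with some low attenders having outcome data. Against this, the dropout list sets these events beside withdrawal and loss of contact without distinction, so ending assessment is the natural reading.
- A reader might infer a bias larger than the whole threshold: 3 of 13 sham participants lost, each 1 SD worse, gives 3/13 = 0.23 SD. That models dropping them, whereas the plan imputes them. It also needs every removal in one arm and none of the gap to be predicted by earlier data. In that example the sham mean improves, so d falls and a go decision becomes less likely.
- A reader might infer that completion merely restates compliance. The article does not define completion, so this cannot be established.
- Other treatment might help those who use it, so the sign of D is not known. Estimating the effect without other care is a defensible question. That stands, but it would have to be chosen openly; the article aims at an ITT-like analysis.
- The trial is a descriptive pilot and sampling error dominates. That limits the consequence. However, the imprecision cannot be removed at 26 participants, whereas this source of missing data can.

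**Conclusion.** The concern holds in a limited form. As written, the rules end, or leave no provision for, outcome assessment of people whom the main analysis does not exclude, and imputation then stands in for values that could have been observed. Bias in d follows only if removal is related to outcome and unbalanced between arms, and it can go either way. Its size cannot be established from the article. On assumed removal rates and gaps it runs from about 0 (balanced removal) through 0.05 to 0.10 SD (20% versus 10%) to about 0.2 SD (25% versus 5% with a 1 SD gap). Only the last case matches the progression threshold, and all are small beside a half-width of about 0.77. That the missingness is informative is a reasonable inference, not a documented fact. The change is worth making because it is cheap and the lost data cannot be recovered later.

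**What to change.** Leave the concomitant-treatment rule, and any decision on study treatment, unchanged. In *Allowed or prohibited concomitant treatment* and *Criteria for dropout*, state that non-compliance, deviation or prohibited treatment does not end outcome assessment. Then:

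- record the event and its date;
- continue the scheduled week 3, 5 and 9 assessments unless consent is withdrawn;
- use the observed values in the FAS, and impute only what is still missing;
- use compliance and deviations only to define the PPS;
- report completion as attendance at the week 5 and week 9 assessments, separately from treatment compliance.

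The cost is a wording change and some additional attendances at visits that are already scheduled; the article shows no budget for them. The downside is that the observed outcomes of deviators include the effect of other care. The PPS remains as the supplementary analysis without them. The article reports that recruitment is under way, so an amendment would help only participants whose assessments are still to come, and the full-scale trial.

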## Outcome measure

### Feasibility outcomes

We will evaluate the feasibility of the study by assessing recruitment, compliance, and completion rates. Acceptability of acupuncture will be also evaluated by investigating effect and safety. The acupuncture treatment will be regarded as an acceptable intervention for a full-scale study if the effect size is greater than 0.2 in at least three of six major symptoms. With respect to safety, a full-scale study will be planned if there is no serious adverse event (SAE) associated with the intervention and if the incidence of adverse events (AEs) is not significantly different from the CG.

The integrity of the study will be examined as a qualitative indicator with regard to whether the study proceeds without any problems and whether a full-scale study is possible without modification of the pilot study design. This will be measured using the Acceptance Checklist for Clinical Effectiveness Pilot Trials (ACCEPT) [31]. We will check the blinding index to determine whether the blinding procedure requires modification. The blinding index ranges from − 1 to 1, with 0 being the most favorable blindness level [32].

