Acupuncture has been used for various psychiatric disorders [16], and its clinical effect against depression [17] and anxiety [18, 19] has been reported in previous studies. For studies on HB, one study reported improvement in the symptoms of HB and Beck Depression Inventory (BDI) score but not in STAXI and State-Trait Anxiety Inventory (STAI) scores [20]. Several studies reported contrasting results, and did not find significant improvement in symptoms of HB or in BDI, STAXI, or STAI scores [21, 22]. These three studies included a control group that received shallow, penetrating, sham acupuncture at non-acupuncture points, which may have contributed to a failure to detect differences between the groups. In addition, the acupuncture used in these studies was focused on traditional eastern philosophy using the Five Elements Theory; thus, the method exhibited limitations in the possible widespread use by global researchers and practitioners. Two studies focused on concurrent symptoms, such as insomnia and anxiety, but remained limited in that one used a waiting list and the other included a single-group, open-trial design [23]. In 2013, clinical guidelines for HB were developed encompassing various studies. The guidelines indicated the limitations as a standardized treatment regimen could not be determined. The clinical guidelines proposed the use of acupuncture to treat HB based on previous evidence and noted that individualized treatment that considers the specific disposition and level and type of stress must be simultaneously provided [24]. Given the need for further research regarding individualized treatment, the present clinical study protocol was developed to use both fixed acupuncture points related to the major symptoms of HB, and variable acupuncture points based on traditional Korean medicine (TKM) principles.

Accordingly, we designed a randomized, sham-controlled, participant- and assessor-blinded, parallel-design pilot study using sham-treatment control and a 1:1 allocation. We will assess the clinical trial feasibility, and explore the effect and safety of acupuncture as a treatment for HB by comparing an experimental group (EG) receiving semi-individualized acupuncture with a control group (CG) receiving sham acupuncture.

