### Sample size calculation

This study aims to evaluate clinical trial feasibility and to investigate basic information about effects and safety of acupuncture for the treatment of HB, rather than to satisfy hypothesis testing. Therefore, the sample size was not decided based on power calculations but based on the precision of mean and standard deviation (SD), the rationale of feasibility, and ethical issues that prohibit over-recruitment of participants. We ensured that the sample size exceeded the minimal number needed to assure the validity of the mean, SD and effect size and rationale of feasibility [25] and considered the study period and research budget [26, 27]. Accordingly, a sample size of 26 participants was estimated.

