## Characteristics of participants

### Inclusion criteria

Men and women who are aged 20 to 65 yearsMeet the diagnostic criteria of the HBDIS: participants should have at least three of the four major symptoms (including chest discomfort, burning sensation of the face or chest, a surge of feeling, and sensation of a mass in the throat or in the epigastrium), one of two major psychological symptoms (including feelings of unfairness and mortification, and emotional resentment or ill will), two of four related somatic symptoms, and two of three related psychological symptoms. The symptoms should be related to stress, should cause psychosocial hypo-function, and should not be caused by a medical disorderProvide written informed consent after being informed of the objectives and details of the clinical trial and agreeing to participate in the trial

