## Discussion

HB, which literally means anger syndrome, leads to both somatic and psychological symptoms. The psychological symptoms mainly include an inadequate expression of anger and trait anger, and the somatic symptoms mainly include palpitations, chest discomfort and gastrointestinal disorders [7, 42, 43]. Regarding the causes of HB, a person’s specific disposition, stress from a difficult marital relationship or a serious life crisis can both act as risk factors of HB; enduring negative emotions for a long period of time is known to be a root cause of HB [44].

Patients with HB tend to avoid psychiatric treatment and to rely on treatments that focus only on their physical symptoms [43, 45]. These patients also receive insufficient social support [42]. Despite relatively high levels of self-awareness of HB among these patients [3, 10, 11], they have been unable to receive effective treatment; therefore, further research is needed to develop more effective and acceptable treatments for HB.

This is a pilot study that aims to evaluate the feasibility of acupuncture treatment for HB and to confirm basic information about its effects and safety [46]. In pilot studies, determining feasibility should be the first priority, and data regarding treatment effects should be descriptively analyzed to avoid exaggerated interpretations [47–51]. Therefore, this trial primarily aims to obtain information about the recruitment, consent, and integrity of the study protocol based on recruitment rate, compliance rate, and completion rate. Clinical effects will be assessed to explore the effects and safety of the intervention and to determine the effect size [47, 52, 53]. We will present Cohen’s *d*, which provides an estimated effect size, because the effect size provides numerical information about the actual difference between two outcomes whereas *p* values are affected by sample size and only provide a dichotomous assessment of statistical significance [54–57]. These data will provide the information needed to calculate the sample size as well as information on the intervention effects that can be easily compared to interventions applied in other studies [38, 47].

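### The efficacy condition for progression (observed d above 0.2 in three of six symptoms) is met in about 27–33% of 26-participant pilots when acupuncture has no effect, so it cannot on its own support the efficacy part of that decision

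*Protocol article*

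**What the plan says.** The section Feasibility outcomes sets a decision rule on efficacy. It judges whether the treatment is fit to be taken into a larger trial, and the answer is yes "if the effect size is greater than 0.2 in at least three of six major symptoms". The six symptoms are the VAS items named as primary under Clinical outcomes (four somatic, two psychological). Statistical analysis defines the effect size as Cohen's d, taken at the end of the 4-week treatment.

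The same section puts other criteria beside this rule. On safety, "a full-scale study will be planned if there is no serious adverse event (SAE) associated with the intervention", and the adverse event incidence must not differ significantly from control. Recruitment, compliance and completion rates, the ACCEPT checklist and the blinding index are also assessed.

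On size, the Sample size calculation section says that "a sample size of 26 participants was estimated". It states that this was not based on power and that hypothesis testing is not the aim. The Background describes a "parallel-design pilot study using sham-treatment control and a 1:1 allocation". The Discussion says that in pilot studies "data regarding treatment effects should be descriptively analyzed to avoid exaggerated interpretations".

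**The concern.** A threshold on an observed d acts as a test, whether or not a p value is attached. It has a false-pass rate and a false-fail rate, and the article states neither. With so few participants the sampling error of d is large against a threshold of 0.2, so chance alone can satisfy the rule.

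The article also takes two positions that do not fit together. The Discussion and the sample size section say that effects are descriptive and that no hypothesis is tested. Feasibility outcomes nevertheless lets the observed effect decide whether the treatment counts as acceptable for a full-scale trial. If the rule is applied as written, an ineffective treatment may be carried forward as having met a pre-specified efficacy criterion, and a treatment with a modest real effect may be recorded as having failed it.

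**Working it through.** **Inputs from the article.** Total 26, allocation 1:1, hence 26/2 = 13 per arm. Rule: d > 0.2 in at least 3 of 6 items. The sample size is expressly not power-based and no error rate is given for the rule, so there is no stated figure to reproduce.

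**Assumptions, not in the article.** d compares the two arms using the pooled SD; only d in favour of acupuncture counts; VAS scores are roughly normal; the true effect is the same on all six items; the six items are equally correlated, with correlation ρ varied because the article gives none.

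**Step 1, precision.** Near zero effect, SE(d) ≈ √(2/n) = √(2/13) = 0.392. The 95% half-width is 1.96 × 0.392 = 0.77. The threshold lies 0.2/0.392 = 0.51 standard errors from zero.

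**Step 2, one item with no effect.** d·√(n/2) follows a t distribution with 2n − 2 = 24 degrees of freedom, so P(d > 0.2) = P(t₂₄ > 0.51) = 0.307.

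**Step 3, three of six with independent items.** Binomial with 6 items and p = 0.307: P(0) = 0.110, P(1) = 0.294, P(2) = 0.326. P(at least 3) = 1 − 0.730 = 0.27.

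**Step 4, correlated items.** Simulation of six equicorrelated normal items, 13 per arm, 100,000 trials per setting. Probability that the condition is met:

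| True d on every item | ρ = 0.3 | ρ = 0.5 | ρ = 0.7 |
|---|---|---|---|
| −0.2 (worse than sham) | 0.11 | 0.13 | 0.15 |
| 0 | 0.31 | 0.32 | 0.33 |
| 0.2 | 0.60 | 0.58 | 0.55 |
| 0.3 | 0.73 | 0.70 | 0.66 |
| 0.5 | 0.91 | 0.88 | 0.84 |

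The miss rate at d = 0.3 is one minus that row, 27–34%. At ρ = 0.9 the row for d = −0.2 reaches 0.16, and the null row is 0.32.

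**Step 5, dropout.** With 10 or 11 evaluable per arm (assumed), the null pass rate is 0.30–0.35 over ρ = 0 to 0.9.

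**Step 6, would another gate do better?** Two alternatives on the mean of the six items, again at 13 per arm:
- Observed d > 0.2 on the mean: passes about 31% under no effect. The false-pass rate therefore comes from the sample size, not from counting three of six.
- Lower 95% limit above zero: stops a true per-item d of 0.5 in about 53–71% of trials (ρ 0.3–0.7), against 9–16% under the current rule.

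**The case against.** The strongest defence is that the rule is a lenient screen and only one element of the decision. Safety conditions, feasibility rates, ACCEPT and the blinding index stand beside it, and a full-scale trial would test efficacy properly. How lenient a pilot screen should be is a design judgement, and a pilot may be small. The rule also separates larger effects: it is met in 84–92% of trials at d = 0.5, against about 32% at zero. All of this stands, and it limits the point to the efficacy component. It does not remove the point, because none of the other criteria tests efficacy and so none can correct a false efficacy pass.

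A reader might infer more than the article supports:

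- *That the whole decision to proceed is a one-in-three chance under no effect.* The figure belongs to one condition. The pass rate of the full set of criteria cannot be derived from the article.
- *That the pilot's main output is unreliable.* Its stated primary aims are recruitment, compliance and completion, and a noisy d leaves those rates untouched.
- *That, since no direction is written, |d| might be used.* The null pass rate would then be far higher, but a treatment that does worse than sham would hardly be called acceptable, so that reading is implausible.
- *That absent symptoms dilute d by a known amount.* Eligibility does allow a missing symptom ("participants should have at least three of the four major symptoms"), but the article does not say how many participants lack each one or what they would score. If each participant lacks at most one of four somatic symptoms, average absence per somatic item is at most 1/4 = 25%. No dilution figure can be fixed from the article.
- *That missing numeric feasibility thresholds are a fault.* The full protocol may hold them.

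**Conclusion.** The point holds for the efficacy condition taken alone. At 13 per arm it is met in about 27–33% of trials when there is no effect (ρ 0 to 0.7) and in 11–16% when acupuncture is worse than sham by 0.2 SD (ρ 0.3 to 0.9). It is missed in 27–34% at a true d of 0.3 (ρ 0.3 to 0.7). It discriminates usefully only at larger effects. A pass or a fail is therefore weak evidence about a small or modest effect, which is the range where a threshold of 0.2 is meant to decide.

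Using it as a pass condition also contradicts the article's own position that effects are descriptive and that hypotheses are not tested. The absence of a power calculation is not the fault. The fault is a pass mark on a point estimate that 26 participants cannot separate from zero.

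The figures rest on the assumptions listed with the calculation: a between-group d counted only in the direction of benefit, approximate normality, a common true effect across items, and an assumed inter-item correlation. Within the range examined, the correlation changes the null figure little.

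**What to change.** In Feasibility outcomes, remove d > 0.2 in three of six symptoms as a pass condition for progression. If the sponsor wishes to keep it, label it supportive only and print its false-pass and false-fail rates beside it. Rest progression on the feasibility and safety criteria already stated there. In Statistical analysis, report the signed between-group d (positive = benefit) with its 95% confidence interval for each of the six VAS items and for their mean.

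Do not substitute a gate requiring the interval for the mean of the six items to exclude zero: at this size it would stop a true d of 0.5 more often than not.

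The change is one of wording, best made before unblinding, and it alters no data collection. The cost is that the sponsor gives up a simple efficacy pass mark.

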This study has some limitations. First, this clinical trial will include a small population of participants and will not primarily aim to perform hypothesis testing. Therefore, the results of this study cannot be generalized as basic data for evaluating the effect and safety of acupuncture for HB. Moreover, because the CG will receive minimal acupuncture, we cannot neglect the possibility of physiological activation caused by needle penetration. The effect of acupuncture will need to be carefully interpreted because the acupuncture points, needling depth, and *de-qi* will be the only differences between groups.

However, as this trial assesses the use of optimized, semi-individualized acupuncture for HB to enable the design of larger RCTs, we expect that it can provide feasibility data and basic information about the effect and safety of acupuncture for HB.

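### The adverse-event half of the safety progression rule is met by a non-significant difference from sham, with no margin, in a 26-person pilot not sized for testing

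*Protocol article*

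**What the plan says.** Under Outcome measure, Feasibility outcomes, the Protocol article gives a two-part safety rule for moving on. The first part is that "a full-scale study will be planned if there is no serious adverse event (SAE) associated with the intervention". The second, joined to it by 'and', is that the same holds "if the incidence of adverse events (AEs) is not significantly different from the CG". The second part comes with no tolerable excess, test, significance level or expected AE rate, and does not say whether incidence is counted per participant or per session.

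On size, Sample size calculation reports that "a sample size of 26 participants was estimated", and Background describes a "parallel-design pilot study using sham-treatment control and a 1:1 allocation", which gives 13 per arm. Sample size calculation also says that "the sample size was not decided based on power calculations" and that the aim is feasibility and basic information "rather than to satisfy hypothesis testing". The Discussion, under limitations, repeats that the trial "will not primarily aim to perform hypothesis testing". Earlier in the Discussion, Cohen's d is preferred because p "values are affected by sample size and only provide a dichotomous assessment of statistical significance".

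**The concern.** A non-significant result can mean that the arms are similar or that the study is too small to tell. With 13 per arm the second explanation is usually available, so a rule that passes on non-significance cannot separate the two. The rule also works backwards: the fewer people randomised or retained, the easier it is to meet. This is the dependence on sample size for which the Discussion sets p values aside on the efficacy side.

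What is at stake is a decision to expose more people. The active arm is needled at 5 to 25 mm with manipulation and the sham arm at 1 to 3 mm without, so an excess of non-serious events in the active arm is plausible. Many of the events listed under Safety issues (local bleeding or haematoma, pain, drowsiness, nausea, headache) will usually be non-serious, and for these the comparison with sham is the only part of the safety rule that applies.

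**Working it through.** **Plan's own figure.** The protocol states no power, significance level or AE rate, so there is no operating characteristic to reproduce. The only input is 26 participants at 1:1, and 26 / 2 = 13 per arm.

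**Assumptions, none stated in the protocol.** The unit is the participant with at least one AE; the test is Fisher's exact test, two-sided 5%; there is no dropout. The AE rates are illustrative.

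**Probability that the clause is met despite a true excess.** With a AE cases among 13 in the acupuncture arm and b among 13 in sham,

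miss rate = 1 - Σ Bin(a; 13, p_acu) × Bin(b; 13, p_sham), summed over all tables (a, b) with p ≤ 0.05.

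| Acupuncture vs sham | Miss rate, Fisher |
|---|---|
| 20% vs 10% | 97% |
| 30% vs 10% | 88% |
| 40% vs 20% | 89% |
| 40% vs 10% | 72% |
| 50% vs 10% | 51% |

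**Sensitivity to the assumed rates, ratio held at four.** 20% vs 5%: 95%. 30% vs 7.5%: 85%. 40% vs 10%: 72%. 50% vs 12.5%: 58%. 60% vs 15%: 42%. 80% vs 20%: 13%.

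**Sensitivity to test and dropout, at 40% vs 10%.** Uncorrected Pearson chi-square: 57%. One-sided Fisher: 57%. Yates-corrected chi-square: 72%. Fisher with 11 per arm: 81%.

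**An observed result that needs no assumed rate: 5/13 vs 1/13.**
- Fisher: C(26,6) = 230,230. P(5 of the 6 cases in acupuncture) = 1,287 × 13 / 230,230 = 0.0727. P(6 of 6) = 1,716 / 230,230 = 0.0075. One tail is 0.0801; the design is symmetric, so two-sided p = 0.160.
- Pearson: pooled rate 6/26 = 0.2308; standard error √(0.2308 × 0.7692 × 2/13) = 0.1653; z = 0.3077 / 0.1653 = 1.86; p = 0.063.
- Difference: 0.3846 - 0.0769 = 0.3077. The Wilson limits are 0.177 to 0.645 for 5/13 and 0.014 to 0.333 for 1/13. Newcombe lower limit: 0.3077 - √(0.2075² + 0.2562²) = -0.022. Upper limit: 0.3077 + √(0.2602² + 0.0632²) = 0.575.

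The clause is met under either test, while the data are compatible with an excess of up to 58 points.

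**Where the Fisher version starts to fail.** With 0 cases in sham, acupuncture needs 5/13 (p = 0.039); 4/13 passes (p = 0.096). With 1 case in sham it needs 7/13 (p = 0.030); 6/13 passes (p = 0.073). With Pearson, 4/13 vs 0/13 (p = 0.030) and 6/13 vs 1/13 (p = 0.027) would fail instead, so in these cases progression turns on a test the protocol does not name.

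**The case against.** **The test, level and unit may be in an analysis plan that is not shown.** This is fair, and their absence is not the finding. It does mean that no single miss rate belongs to the design. A reader might infer that the trial misses a fourfold excess about 72% of the time. The documents do not support that: the figure needs 40% vs 10%, Fisher or Yates, two-sided 5%, participants as the unit and full follow-up. Counting sessions instead (10 × 13 = 130 per arm) would give different figures. What stands is that naming a test would not turn non-significance into evidence of similarity.

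**The clause is only half of the rule.** A reader might infer that the whole safety gate is passed by default. That is not supported: the same sentence requires no intervention-related SAE, Safety issues provides for recording causality and severity and for halting the study on an SAE, and very large AE excesses would usually be flagged. Other feasibility criteria also bear on progression. These limit the consequence, but none assesses an excess of non-serious events.

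**The rule governs planning and does not declare safety.** A reader might infer that a pass would be reported as showing that acupuncture is safe. The text says only that a larger study will be planned, and the limitations paragraph warns against generalising the safety results. The objection stands; the defect lies in the progression criterion.

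**The protocol does not rule out all testing.** Sample size calculation explains how the number was chosen, and the Discussion says only that testing is not the primary aim. A secondary test is therefore not a flat contradiction. It still sits badly with the protocol's own reason for preferring effect sizes.

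**Fewer AEs with acupuncture would also fail the rule.** This is true of the literal, non-directional wording, but remote given the needling depths: under 0.1 percentage point of probability in the Fisher scenarios above. It is a minor point.

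**Conclusion.** The concern holds for the AE condition. It makes a non-significant difference from sham, with no margin, a requirement for going on, in a study that was not sized to detect one. Under the stated assumptions, the doublings and triplings examined (20% vs 10%, 40% vs 20%, 30% vs 10%) are missed about 88% to 97% of the time. Fourfold excesses are missed between 13% and 95% of the time, depending on the sham rate. The 5/13 vs 1/13 example is firmer, because it uses no assumed rate and passes under both common tests.

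This is a criterion stated wrongly, not a detail left for later. Because the SAE condition stands beside it and the rule decides only whether a larger trial is planned, it is a should-fix point, not one that invalidates the pilot.

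**What to change.** Keep the SAE condition as it is. Replace the AE clause with the following:

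- Per arm, report the number and percentage of participants with at least one AE, and with at least one intervention-related AE.
- Give the between-arm difference for each with a 95% CI (Newcombe).
- Judge that difference and its interval against an acceptable limit that the sponsor sets and records before unblinding, and say whether the estimate or the upper confidence limit is compared with it. A limit on excess in the acupuncture arm also removes the non-directional wording.
- State that no significance test decides progression.

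The cost is a wording change in the protocol and analysis plan, with no new data or participants. The sponsor must commit to a limit, and with 13 per arm the interval will be wide: in the example above it spans about 60 points (-2 to 58). That width is the uncertainty the present rule conceals.
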